## Abstract

**Background::**

Surgery is the only potentially curative treatment for gastric cancer, however, it bears a high postoperative morbidity and mortality rate. A recent randomized control trial proposed prehabilitation to reduce the postoperative morbidity in patients undergoing major abdominal surgery. Currently, there is a lack of evidence of using prehabilitation for patients undergoing gastrectomy for gastric cancer. The aim of our study is to demonstrate that home-based prehabilitation can reduce postoperative morbidity after gastrectomy for gastric cancer.

**Methods::**

PREFOG is a multi-center, open-label randomized control trial comparing 90-days postoperative morbidity rate after gastrectomy for gastric cancer between patients with or without prehabilitation. One-hundred twenty-eight patients will be randomized into an intervention or control group. The intervention arm will receive trimodal home-based prehabilitation including nutritional, psychological and exercise interventions. Secondary outcomes of the study will include physical and nutritional status, anxiety and depression level, quality of life, postoperative mortality rates and full completion of the oncological treatment as determined by the multidisciplinary tumor board.

**Discussion::**

PREFOG study will show if home-based trimodal prehabilitation is effective to reduce postoperative morbidity after gastrectomy for gastric cancer. Moreover, this study will allow us to determine whether prehabilitation can improve physical fitness and activity levels, nutritional status and quality of life as well as reducing anxiety and depression levels after gastrectomy for gastric cancer.

**Trial registration::**

ClinicalTrials.gov NCT04223401 (First posted: 10 January 2020).

## Introduction

1

Surgery is the main and only curative treatment option for gastric cancer (GC).^[1]^ Despite the progress in surgical and anesthetic techniques, gastrectomy remains associated with high postoperative morbidity (∼50%) and mortality (∼5%) rates.^[2–4]^ Furthermore, patients suffering postoperative complications are less likely to receive adjuvant therapy or must delay the initiation of it^[5,6]^ and it impairs the long-term outcomes.^[7]^ Therefore, there is a great need for novel strategies to reduce the postoperative morbidity after gastrectomy for GC.

Poor physical condition (determined by cardiopulmonary exercise testing), sarcopenia, and preoperative malnutrition often accompanies GC and represents decreased physiological reserve, predicting postoperative complications.^[4,8,9]^ Moreover, the majority of patients with resectable GC are considered for perioperative chemotherapy which improves oncological outcomes but impairs patients’ physical fitness before the surgery.^[10,11]^ Some patients’ risk factors are modifiable and may be improved within several weeks before surgery by a short multimodal prehabilitation consisting of physical training, nutritional adjustments and psychological support.^[12–14]^ Besides improved physical and nutritional status attributed to prehabilitation, a recent randomized control trial (RCT) showed a 51% reduction of postoperative complications after major abdominal surgery.^[15]^ Given the high morbidity rate, poor initial physical and nutritional status and the need for preoperative chemotherapy, GC patients would be ideal candidates to receive prehabilitation. To date, several studies already investigated the role of prehabilitation in esophagogastric surgery.^[16]^ However, most of these focused on patients receiving esophagectomy, with limited data for gastrectomy.^[16]^ A match pair analysis study showed reduced postoperative morbidity following prehabilitation in patients with GC and metabolic syndrome,^[17]^ while a small pilot study found increased physical status in elderly sarcopenic GC patients.^[18]^ However, these studies were rather small and inconclusive. There is a need for an RCT to address the role of prehabilitation in GC surgery.

The aim of this study is to demonstrate reduced postoperative morbidity after gastrectomy for GC in patients who undergo home-based prehabilitation.

## Methods

2

### Study setting and trial design

2.1

This multicenter study is designed as a prospective, parallel-group, 1:1 randomized control, open-label trial. The study will be conducted at two major gastrointestinal cancer treatment centers of Lithuania: National Cancer Institute and Vilnius University hospital Santaros Klinikos. A study flowchart is provided in Figure 1. Data collection and follow-up schedules are shown in Table 1.

**Figure 1 F1:**
[figure not shown]
Consort diagram: flow chart.

**Table 1 T1:**
[figure not shown]
Standard protocol items: recommendations for interventional trials (SPIRIT) figure. Flowchart of the PREhabilitation FOr Gastrectomy (PREFOG) trial.

### Eligibility criteria

2.2

The study will include gastric cancer patients scheduled for elective total or subtotal gastrectomy at multidisciplinary team meetings. Patients scheduled for gastrectomy first and gastrectomy after neoadjuvant chemotherapy are eligible. Participants will be included after screening for eligibility and obtaining written informed consent. To participate in the study candidates must meet the following inclusion criteria:

1.Age ≥ 18 years.2.Patient agrees to participate in a clinical study.3.Patient requires surgical treatment for gastric cancer.

Patients will be excluded if they meet the following criteria:

1.Patient requires surgical treatment for gastric cancer recurrence.2.Patient condition not allowing to postpone surgery for at least 4 weeks.3.Patients’ physical or mental condition that does not allow the patient to participate in the prehabilitation program.

### Interventions

2.3

#### Control group

2.3.1

The control (standard of care) group will receive routine care from their gastric cancer diagnosis to surgical treatment. These patients will receive no specific advice for prehabilitation before surgery except a recommendation for nutritional supplements by high-energy drinks on the decision of the surgeon.

#### Prehabilitation group

2.3.2

The prehabilitation (intervention) group will receive home-based trimodal prehabilitation before the gastrectomy. The prehabilitation will consist of:

1) *Exercise intervention:* Patients will be consulted by physical medicine and rehabilitation physicians and physiotherapists to develop personalized home-based exercise program according to a physical performance examination and results of spiroergometry. All patients will undergo three supervised training sessions where they will be trained in correct exercise techniques and self-control in training intensity. Additionally, each patient will receive a written exercise program with detailed description of it. The home-based program will consist of 4 types of exercises:

Endurance training for 10 to 30 minutes daily by walking/stair climbing/dancing/water exercises/biking. The type of exercise will depend on the patient's choice. The target intensity is 40% to 65% of the heart rate reserve.Respiratory muscles training for 5 to 10 minutes daily.Resistance training to improve muscular strength for 10 to 20 minutes 3 times per week.Stretching exercises for 5 to 10 minutes 3 times per week.

In total daily training sessions will not exceed 60 minutes.

2) *Nutritional support:* A dietician will perform a physical examination and bioimpedance to evaluate the nutritional status of each patient and will provide personalized recommendations for the prevention or correction of malnutrition. The energy and protein requirements will be estimated with 25 to 30 kcal/kg and 1.5 g/kg of ideal body weight respectively. If necessary, patients will be prescribed to consume oral nutritional supplements to increase the consumption of calories and proteins.

3) *Psychological support:* Patients will undergo consultation by specialized onco-psychologist. The anxiety and depression level will be evaluated by the HAD score and patients will be trained to perform relaxation techniques to reduce and manage anxiety at home.

The total length of the prehabilitation program will depend on the gastric cancer treatment pathway. Patients scheduled for the gastrectomy first will undergo prehabilitation for 4 weeks before surgery. Patients scheduled for neoadjuvant chemotherapy first will receive prehabilitation through the entire time of neoadjuvant treatment. The length of the prehabilitation will depend on the neoadjuvant chemotherapy scheme, which is chosen by medical oncologists irrespective of participation in the study.

### Strategies to improve adherence to interventions

2.4

To increase compliance with the prehabilitation program patients will be asked to fill a diary to record their daily prehabilitation practice. Also, the study staff will contact the patient to inquire about the adherence to the study protocol weekly by the phone call.

### Study outcomes

2.5

#### Primary endpoint

2.5.1

The primary outcome of the study is the postoperative morbidity rate by the Clavien-Dindo classification at 90 days postoperatively. All postoperative complications will be recorded at the time of discharge and the surgeon will document any events after discharge at the outpatient appointment 90 days postoperatively. All complications will be classified by the Clavien-Dindo classification.

#### Secondary endpoints

2.5.2

The secondary endpoints include:

1)Postoperative intrahospital and 90-day mortality rate2)Postoperative intrahospital and 30-day morbidity rate3)Physical status of the patient at baseline, pre-surgery, at discharge and 12 months after surgery by:Six-minute walk testSpiroergometry (VO_2,_ VO_2max_, AT)Grip strength testSit to stand testTimed up and go testThoracic excursion testInternational Physical Activity Questionnaire (IPAQ) score.4)Nutritional status at baseline, pre-surgery, 3, 6 and 12 months after surgery by:Blood albumin levelBioimpedanceNutritional Risk Score-2002 questionnaire score (NRS2002)5)Quality of Life at baseline, pre-surgery, 3, 6, and 12 months after surgery by:EORTC QLQ-C30 and STO-22 questionnaires scores6)Anxiety and depression level at baseline, pre-surgery, 3, 6 and 12 months after surgery by:Hospital anxiety and depression scale (HADS) score7)The proportion of patients completing the oncological treatment fixed in a multidisciplinary tumor board (including preoperative chemotherapy, surgery, and postoperative chemotherapy) at 12 months after treatment initiation

#### Other objectives and supplementary data collected

2.5.3

Additionally, we will collect data regarding patient demographics, clinical variables (i.e., age and gender, smoking, alcohol usage), surgical and anesthetic details (i.e., intensive care unit and hospital length of stay, type and length of surgery, blood loss, intraoperative complications, t. protein and CRP levels) and disease-related parameters (i.e., stage of disease by TNM classification, tumor regression grade by Becker classification). Study data will be collected and managed using case report forms (CRF).

### Biobanking

2.6

Additional informed consent may be taken from patients for the biobanking of blood, urine and tissue samples as a part of daily practice in the study institutions. These samples may be used for future laboratory, genetic or molecular analysis.

### Data collection and management

2.7

All the data will be recorded in CRFs, to maintain the confidentiality all personal data will be coded. Data will be collected at baseline, preoperatively, during the intrahospital period (preoperatively and postoperatively) and after discharge (up until 12 months after surgery).

### Recruitment

2.8

All gastric cancer patients discussed at the multidisciplinary tumor board meetings in the participating institutions are screened for eligibility for the study. Potentially eligible patients are approached with written informed consent at the outpatient visit to the surgeon. Patient recruitment started at February 2020. Twenty-two months are planned for the recruitment and 300 patients are anticipated to undergo gastrectomy at the study institutions within this time. Therefore, the recruitment of 128 patients seems to be feasible.

### Assignment of interventions: allocation

2.9

#### Sequence generation

2.9.1

Participants will be randomly assigned to either control or experimental group with a 1:1 allocation as per a computer-generated randomization schedule stratified by neoadjuvant treatment using random permuted blocks of 4 and 6. The randomization sequence was created using an online available free tool (https://www.sealedenvelope.com/).

#### Concealment mechanism and implementation

2.9.2

The researcher assistant will prepare sequentially numbered, opaque, sealed envelopes containing randomization sheets. To distinguish patients receiving perioperative chemotherapy, the envelopes will be additionally marked. The randomization sheet will report the randomization code and assigned treatment (standard of care or prehabilitation). The prepared and sealed envelopes will be split into equal piles and delivered to the dedicated place in both study centers. At the time of randomization, the investigator (surgeon consulting the patient) will choose an envelope with the lowest number and will write the name and date of birth of the participant before opening to prevent subversion of the allocation sequence. After opening, the randomization information will be given to the patient, the baseline condition of the patient will be assessed and the case report form (CRF) will be filled in.

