### Sample size

2.10

The sample size calculation was done using G∗Power 3.1.9.4 software using the reduction of 90 days postoperative complication rates as the primary outcome. Based on the assumption that the percentage of patients developing postoperative complications after gastrectomy is approximately 50% for the control group (based on our centers historical experience and results from RCTs)^[2,3]^ and can be reduced to 25% in the prehabilitation group (based on results of recent RCT showing 50% reduction of postoperative complications by prehabilitation),^[15]^ a group sample size of 58 patients is needed to achieve 80% power in detecting this difference in 90-days postoperative morbidity at a two-sided level of significance of 5%. Under the assumption of a drop-out rate of up to 10%, a total of 128 patients (64 per group) needs to be enrolled in the study.

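### Envelopes from a schedule stratified only by neoadjuvant treatment are split into equal piles for two centres with no rule keeping blocks whole, so arms can be unbalanced within centre, and the primary test does not use centre

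*Protocol article*

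**What the plan says.** All references are to the protocol article.

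- **Study setting and trial design (2.1):** "The study will be conducted at two major gastrointestinal cancer treatment centers of Lithuania".
- **Sequence generation (2.9.1):** allocation is 1:1 from a "computer-generated randomization schedule stratified by neoadjuvant treatment using random permuted blocks of 4 and 6". Centre is not a stratification factor.
- **Concealment mechanism and implementation (2.9.2):** the envelopes are sequentially numbered. On the strata: "To distinguish patients receiving perioperative chemotherapy, the envelopes will be additionally marked". Then: "The prepared and sealed envelopes will be split into equal piles and delivered to the dedicated place in both study centers". At each randomisation the surgeon "will choose an envelope with the lowest number".
- **Statistical analysis (2.11):** the primary outcome is compared with a Chi-Square test. No stratification of that test is named.

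The article does not say whether the piles follow block boundaries, whether each centre has its own list, or how many envelopes were prepared.

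**The concern.** Permuted blocks balance the arms only where whole blocks are used in sequence. Here the blocks are built for the trial as a whole, within neoadjuvant stratum, and the finished envelopes are then divided between two places. If neighbouring envelopes go to different centres, most blocks are broken and neither centre's sequence is balanced by design. If each list is cut in the middle, at most one block per stratum is broken.

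Equal piles also fit only equal recruitment. Section 2.8 (Recruitment) gives an anticipated total for the two institutions together and no figure by centre. If the centres recruit unequally and one pile is left partly unused, the halves of broken blocks no longer offset each other and the overall 1:1 balance can drift as well.

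At stake is chance confounding of treatment with centre. If complication rates differ between the centres, a within-centre arm imbalance moves part of that difference into the crude treatment contrast, and an unstratified test does not take it out.

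**Working it through.** **1. The plan's own sample size.** Inputs from section 2.10: the complication rate "is approximately 50% for the control group" and "can be reduced to 25% in the prehabilitation group", two-sided 5%, 80% power. The two-proportion formula without continuity correction gives 58 per group (power at 58 is 0.802), as stated. The allowance for drop-out is 58 × 1.1 = 63.8, so 64 per group and 128 in total, also as stated. These figures are not in dispute; 128 is used below.

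**2. Simulation of the split.** From the documents: 1:1, blocks of 4 and 6, two neoadjuvant strata, two centres, equal piles, lowest number first, 128 patients. Assumed, because the documents do not say: block sizes 4 and 6 equally likely, 64 patients in each stratum, 64 patients at each centre, all envelopes used. For each simulated trial, D = |prehabilitation − control| among one centre's 64 patients. About 10,000 trials per rule:

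| How the piles are made | Mean D | D of 10 or more |
|---|---|---|
| Dealt alternately | 5.0 | about 15% |
| Shuffled, then divided | about 4.5 | about 11% |
| Each list halved consecutively | 0.8 (first half) to 1.3 (second half) | 0% (maximum 8) |
| Separate list per centre and stratum | 0.8 | 0% (maximum 4) |

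Taking the worse of the two centres, the mean is 5.4 under alternate dealing, 1.5 under consecutive halves and 1.3 under separate lists. A difference of 6 or more occurs in 47%, 1% and 0% of trials respectively.

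**3. Unequal recruitment.** Assume centre shares of 35% and 65%, with 128 envelopes prepared per stratum so that some stay unused. Under alternate dealing the worse-centre mean rises to 6.7 (95th percentile 14). The overall arm difference averages 4.0 (95th percentile 10), against 0.8 when both piles are used equally. Under consecutive halves the overall difference averages 1.7, and under separate lists 1.3.

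**4. Effect on the treatment contrast.** With 64 per arm and 64 per centre, an arm difference of D within one centre means that the arms differ by D/64 in the share of patients from that centre. If the centres' complication rates differ by Δ, the crude contrast shifts by Δ × D/64. The documents give no Δ; for illustration take 20 points.

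- D = 5: 20 × 5/64 = 1.6 points.
- D = 10: 20 × 10/64 = 3.1 points.

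For scale, the planned effect is 50 − 25 = 25 points. Its standard error at 64 per arm is √[(0.50 × 0.50 + 0.25 × 0.75)/64] = √(0.4375/64) = 0.083, or 8.3 points. The shift can go in either direction.

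**The case against.** Much of the case on the other side stands.

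- **The splitting rule is unknown.** Cutting a sequentially numbered stack in two is at least as natural a reading as dealing it out, and the imbalance is then trivial. A reader might infer that the arms will be unbalanced within centre. The documents do not support that; they support only that imbalance is possible and nothing stated prevents it.
- **An article condenses.** The full protocol may describe the apportioning of envelopes, so silence on that detail is not a fault. What remains is a stated step, equal piles from a schedule "stratified by neoadjuvant treatment using random permuted blocks of 4 and 6", which does not itself secure balance by centre.
- **No bias follows.** A reader might infer that a centre difference would bias the result or inflate the type I error. It would not: assignment is random however the piles are made. Simple randomisation of 64 patients would give a mean absolute arm difference of √(2 × 64/π) ≈ 6.4, so even alternate dealing (5.0) is no worse than an accepted method.
- **Further inferences lack support.** A reader might suppose that the busier centre will exhaust a pile and borrow envelopes, or that the centres do differ in care or in recording complications. The article gives no envelope count, no recruitment by centre and no centre-specific rates, and sets one complication classification for the whole trial. Nor is there literally a single list: the marked envelopes imply one sequence per neoadjuvant stratum.
- **Stratifying by centre is optional** in a two-centre trial of this size, and a separate analysis plan may already adjust for centre.

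These points limit the size of the problem. They do not alter the fact that the stated method gives up, at no gain, a balance that the same tool could secure.

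**Conclusion.** The point holds as a conditional one. The stated scheme neither stratifies by centre nor keeps blocks whole within a centre, and the stated primary test does not use centre. Under the assumed 64 patients per stratum and per centre, the mean within-centre arm difference ranges from about 1 patient (consecutive halves) to about 5 (alternate dealing, with 10 or more in about 15% of trials). Overall balance suffers appreciably only if the piles are dealt and the centres recruit unequally.

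The cost is chance imbalance and some loss of precision. With an assumed 20-point centre difference, the shift is about 1.6 to 3.1 points for imbalances of 5 to 10 patients, small beside a standard error of 8.3 points. This is a worthwhile, low-priority improvement and does not call the trial's validity into question.

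**What to change.** 1. **Randomisation, for any recruitment that remains.** Generate a separate block list for each centre by neoadjuvant stratum (four lists), or assign whole blocks to each centre. Number the envelopes within list, prepare a surplus in each, and do not transfer envelopes between centres. Recruitment began in February 2020 with 22 months planned, so this step may no longer apply.
2. **Reporting.** Where envelopes have already been used, state how the piles were split.
3. **Analysis, in any case.** Stratify the primary comparison by centre and neoadjuvant treatment, for example with a Cochran-Mantel-Haenszel test, and specify this before outcome data by arm are examined.

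The cost is a few hours to regenerate envelopes and a short amendment. Four lists leave a few more incomplete blocks: in the simulation with equal recruitment, the mean overall arm difference is 1.3 patients (maximum 8), against 0.8 (maximum 4) when both piles of the present schedule are fully used. The sample size stays at 128.

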#### Blinding

2.9.3

The study cannot be blinded because participation in a prehabilitation program cannot be hidden from neither patients nor practitioners.

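### Baseline is assessed after the envelope is opened and the patient told the arm, which exposes the self-reported and effort-dependent baselines of the secondary endpoints to knowledge of allocation

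*Protocol article*

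**What the plan says.** Section 2.9.2 of the protocol article describes the envelope procedure. The person who randomises is the treating surgeon: "the investigator (surgeon consulting the patient) will choose an envelope with the lowest number". The patient's name and date of birth are written on the envelope, and it is opened. The text continues: "After opening, the randomization information will be given to the patient, the baseline condition of the patient will be assessed", and the CRF is then filled in.

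Section 2.9.3 states that there is no blinding: "The study cannot be blinded because participation in a prehabilitation program cannot be hidden from neither patients nor practitioners".

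Section 2.5.2 lists a baseline value for four groups of secondary endpoints:

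- "Physical status of the patient at baseline, pre-surgery, at discharge and 12 months after surgery by": six-minute walk, spiroergometry, grip strength, sit to stand, timed up and go, thoracic excursion and IPAQ.
- "Nutritional status at baseline, pre-surgery, 3, 6 and 12 months after surgery by": albumin, bioimpedance and NRS2002.
- "Quality of Life at baseline, pre-surgery, 3, 6, and 12 months after surgery by": EORTC QLQ-C30 and STO-22.
- "Anxiety and depression level at baseline, pre-surgery, 3, 6 and 12 months after surgery": HADS.

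Section 2.11 names two-group tests for the secondary endpoints and leaves room for other methods if needed. It does not say whether the baseline value enters any of these comparisons.

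**The concern.** A baseline taken before randomisation cannot depend on the arm. One taken after disclosure can. A patient who has just learned that they will, or will not, receive exercise training and psychological support may answer an anxiety or quality-of-life questionnaire differently, or try harder or less hard on a walk or grip test. Staff who know the arm may also encourage differently. The direction cannot be predicted, so the effect cannot be removed afterwards.

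Three uses of the baseline are at stake: change from baseline, baseline-adjusted comparison, and the rows of the baseline table that show these measures. There is also a risk of missing data, since a patient who withdraws on hearing the allocation may leave no baseline at all.

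The abstract and the discussion (section 3) say the trial will determine whether prehabilitation improves fitness, nutritional status and quality of life and reduces anxiety and depression. Such statements invite comparisons that use the baseline.

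**Working it through.** **Order of events.** Section 2.9.2 gives: envelope opened, patient told, baseline assessed, CRF filled in. Section 2.9.3 rules out blinding of patients and practitioners. Section 2.7 lists baseline as a data collection time without placing it relative to allocation. Section 2.3.2 describes a physical performance examination, spiroergometry, bioimpedance and HADS within the prehabilitation work-up, which can only follow allocation. No visible text places a baseline measurement before allocation or gives it to an assessor unaware of the arm.

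**Which endpoints are exposed.**

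| Endpoint or measure | Baseline value? | Open to influence by knowledge of the arm |
|---|---|---|
| 90-day morbidity (primary) | no | not applicable |
| Mortality, in-hospital and 30-day morbidity, treatment completion | no | not applicable |
| HADS, QLQ-C30/STO-22, IPAQ | yes | yes, self-reported |
| Six-minute walk, grip, sit to stand, timed up and go, spiroergometry | yes | yes, effort-dependent |
| Albumin, bioimpedance | yes | unlikely to move much |

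**Size, for illustration only.** The plan states no figure on this point. The group size of 58 comes from section 2.10 and reproduces. With 50% against 25%, two-sided 5% and 80% power, n = [1.960 × √(2 × 0.375 × 0.625) + 0.842 × √(0.25 + 0.1875)]² / 0.25² = 57.7, so 58 per group. Nothing in this point changes that figure.

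Assumed inputs, not in the documents:

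- b, the allocation-induced baseline shift in one arm: 0.1 to 0.3 SD.
- r, the baseline to follow-up correlation: 0.5 to 0.7, with equal SDs at both times.
- No true treatment effect, and no part of the shift left at follow-up.

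Formulas, in SD units:

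- Change score: size of bias = b. Standard error = √(2(1 − r)) × √(2/58).
- Baseline-adjusted: size of bias = r × b. Standard error = √(1 − r²) × √(2/58).
- Follow-up values alone: bias from the baseline shift = 0.

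Here √(2/58) = 0.186. The false-positive rate is the chance that a two-sided 5% test rejects when its mean is displaced by bias divided by standard error.

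| b | r | Change-score bias | False-positive rate | Adjusted bias | False-positive rate |
|---|---|---|---|---|---|
| 0.1 | 0.5 | 0.10 | 8.4% | 0.05 | 6.1% |
| 0.1 | 0.7 | 0.10 | 10.7% | 0.07 | 8.2% |
| 0.2 | 0.5 | 0.20 | 19.0% | 0.10 | 9.5% |
| 0.2 | 0.7 | 0.20 | 28.5% | 0.14 | 18.4% |
| 0.3 | 0.5 | 0.30 | 36.5% | 0.15 | 15.4% |
| 0.3 | 0.7 | 0.30 | 55.0% | 0.21 | 35.4% |

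Worked line for b = 0.2, r = 0.5, change score: the standard error is 1 × 0.186, and 0.2/0.186 = 1.08. The rejection probability is then about 19%.

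**If part of the shift persists.** Let a fraction k of the shift remain at follow-up. The change-score bias becomes (1 − k) × b and the size of the adjusted bias |k − r| × b. At k = 1 the change-score bias is zero. The table is therefore the case k = 0.

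**The case against.** The strongest objection is that nothing here touches the main result. The primary endpoint has no baseline, is tested by a Chi-Square test, and alone determines the sample size. That stands.

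Next, the harm depends on an analysis the article does not specify. Section 2.11 names only two-group tests, and a comparison of follow-up values is free of any baseline shift. That also stands, so the bias is conditional. The size of the shift is assumed and unsigned, and in an open-label trial a reporting effect may persist and partly cancel in a change score. The table is thus an illustration and not an estimate.

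Section 2.9.2 is also a condensed account of envelope logistics. It names none of the tests in section 2.5.2, and the schedule in Table 1 and the flow chart in Figure 1 are not shown. This lowers confidence, but the visible order is explicit. If Table 1 times baseline before allocation, the two places conflict and still need reconciling.

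A reader might infer more than the text supports:

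- That every baseline value is compromised. Albumin and bioimpedance are neither self-reported nor effort-dependent.
- That the baseline table no longer shows whether randomisation worked. Age, gender and tumour stage do not change because an envelope is opened.
- That the baselines are taken after treatment has begun. The text places them after allocation, but not after the start of prehabilitation.
- That the arms are measured in different settings. Section 2.3.2 describes the intervention and does not say where controls are assessed.

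**Conclusion.** The point holds as a procedural weakness confined to secondary endpoints. As written, section 2.9.2 makes the self-reported and effort-dependent baselines post-randomisation values obtained when patient and surgeon know the arm, and it risks missing baselines among patients who withdraw on learning the arm. The primary endpoint, mortality, morbidity and treatment completion are unaffected.

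Bias follows only if the baseline is used for change scores, for adjustment or for the affected rows of the baseline table. Under the assumptions in the working, it is 0.1 to 0.3 SD for a change score and about 0.05 to 0.21 SD for a baseline-adjusted comparison. The actual size cannot be derived from the documents.

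The correction is worth making promptly, because a baseline taken after allocation cannot be retaken. It is not a condition for the validity of the primary analysis. Confidence is moderate because the schedule table is not shown.

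**What to change.** Reorder section 2.9.2: consent; then the baseline assessments and the baseline CRF; then the name on the next envelope; then opening and disclosure. Check the new order against Table 1 and make the two agree.

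Recruitment began in February 2020 (section 2.8), so some patients may already have post-allocation baselines. Flag these in the data set and add, for the affected endpoints, a comparison of follow-up values between arms that does not use them. Do not exclude the patients: if section 2.9.2 was followed, exclusion would remove everyone enrolled before the amendment. The added comparison removes the effect of a shifted baseline, but not open-label influence on the follow-up measurements themselves.

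The cost is a short procedural amendment. No test is added and the sample size does not change. The envelope opening may have to be separated from the surgeon's consultation, with minor rescheduling of baseline tests at both centres. That rescheduling should be checked against the preoperative timeline in section 2.3.2.
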